### Randomization

Randomization will be based on computer-generated allocation, and random numbers will be concealed in opaque envelopes. After intubation, the envelope corresponding to a number in the randomization table will be opened, and the participant will be randomly assigned to either the ultrasound-guided lumbar block group or the control group at a 1:1 allocation ratio according to random number.

### Blinding

Due to the nature of our trial, it is not possible for the anesthesiologist who performs intraoperative anesthetic care to be blinded to the allocation. To minimize the possible bias, we will divide the research staff into two teams. Unblinded team: the anesthesiologist who performs intraoperative anesthetic care will know the assignment. The anesthesiologist is skilled in ultrasound-guided nerve block. The nerve block details will be recorded by the anesthesiologist and placed in a sealed envelope that will only be opened if medically necessary and at the completion of study. The anesthesiologist will not be involved in the outcome assessment. Blinded team: patients, parents, surgeons, assessment investigators, the medical staff who provide postoperative care in the postanesthesia care unit (PACU), data collectors, and statisticians will all be blinded to the group allocation.

### Study time

This study began in May 2017 and has been completed in October 2018. The study was conducted at Shanghai Sixth People's Hospital affiliated with Shanghai Jiao Tong University.

### Interventions

All patients will refrain from solid foods for 6 h and clear fluids for 2 h preoperatively. After intravenous access is established for all patients, standard monitoring—including electrocardiography (ECG), noninvasive blood pressure, and pulse oximetry (SpO_2_)—will be performed and recorded. The values of the heart rate, noninvasive blood pressure, and respiratory rate before anesthesia induction will be recorded as baseline values. During the intraoperative period, inspiratory and expiratory gas analysis and end-tidal carbon dioxide will also be monitored. All values will be recorded every 5 min. General anesthesia will be induced with 0.1 mg/kg midazolam, 2 μg/kg fentanyl, 3 mg/kg propofol, and 0.1 mg/kg vecuronium intravenously. Patients will be intubated endotracheally, and mechanical ventilation will be controlled to maintain end-tidal carbon dioxide at 35–40 mmHg. During the operation, anesthesia will be maintained with 60% nitrous oxide, 40% oxygen, and 2% end-tidal sevoflurane. After anesthesia induction, all children will be assigned to either the ultrasound-guided lumbar plexus block group or the control group according to the randomization table.

### Consort flowchart subject enrollment

The trial flow diagram is presented in Fig. 2.

**Fig. 2 Fig2:**
[figure not shown]
CONSORT flowchart of subject enrollment. CHEOPS Children’s Hospital of Eastern Ontario Pain Scale, PACU postanesthesia care unit, PAED Pediatric Anesthesia Emergence Delirium

### Ultrasound-guided lumbar plexus block group

Patients assigned to ultrasound-guided lumbar plexus block group will be placed in a lateral decubitus position with the hips flexed and the operative site facing upward. The S-Nerve™ Ultrasound System (Sonosite Inc., Bothell, WA, USA) will be used for the ultrasound scan. After aseptic preparation of the lumbar region and transducer, nerve block will be performed with a linear array (6–13 MHz) transducer using the longitudinal approach. All blocks will be performed by the same anesthesiologist experienced and qualified in ultrasound-guided lumbar plexus block. All investigators are trained at the beginning of the study to ensure a standardized intervention and minimize the potential bias.

A line will be drawn to connect the iliac crests and identify the fourth lumbar spine. The ultrasound probe will be placed lateral and parallel to the long axis of the spine at the level of L3–L4. The entry site will be 1.5–2 cm lateral to the midline along the intercristal line. The needle will be advanced cautiously perpendicular to the skin with ultrasound guidance until the tip of the needle reaches 1–1.5 cm below the space between the transverse processes of L3 and L4. To avoid a possible vascular puncture, repeated negative aspirations will be performed during all needle advancements. The lumbar transverse processes exhibit a hyperechoic reflection and acoustic shadows on ultrasound scans, which can produce a ‘trident sign’. The roots of the lumbar plexus are located in the posterior portion of the psoas muscle 1–1.5 cm below the space between the transverse processes. When the needle is in place, 1 ml/kg of 0.2% ropivacaine (Naropin 10 mg/ml; AstraZeneca, Wilmington, DE, USA) will be injected. The maximum dose of local anesthetic is limited to 20 ml, and the injection speed of ropivacaine will be approximately 1 ml/s.

The adequacy of the ultrasound-guided lumbar plexus block will be defined by the visualization of the needle tip in the correct position; the spread of local anesthetic around the lumbar plexus nerves; increases in the heart rate, blood pressure, and respiratory rate of less than 15% in response to the skin incision; and increases in the intraoperative heart rate, blood pressure, and respiratory rate of less than 25%.

The operation will be performed at least 15 min after the nerve block. During the operation, anesthesia will be maintained with 60% nitrous oxide, 40% oxygen, and 2% end-tidal sevoflurane. If the increases in heart rate, noninvasive blood pressure, and respiratory rate are greater than 15% from the baseline the values during the operation, the concentration of sevoflurane will be increased by 0.5%. Conversely, if the reductions in heart rate, noninvasive blood pressure, and respiratory rate are greater than 15% of the baseline values during the operation, the concentration of sevoflurane will be reduced by 0.5% [23]. If additional fentanyl is required when the heart rate, blood pressure, and respiratory rate increase by greater than 25% intraoperatively, the patient will be recorded as a failure or an inadequate lumbar plexus block and also be followed up. Immediate complications will be recorded and treated.

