### Control group

Children assigned to the control group will receive a bolus injection of 1 μg/kg fentanyl intravenously before skin incision. During the operation, anesthesia will be maintained with 60% nitrous oxide, 40% oxygen, and 2% end-tidal sevoflurane. If the increases in the heart rate, noninvasive blood pressure, and respiratory rate are greater than 15% of the baseline values during the operation, then the concentration of sevoflurane will be increased by 0.5%. Conversely, if the heart rate, noninvasive blood pressure, and respiratory rate are reduced by greater than 15% of the baseline values during the operation, then the concentration of sevoflurane will be decreased by 0.5%. Furthermore, if the heart rate, blood pressure, and respiratory rate increase by greater than 25% of the baseline values during the surgery, then children will receive an additional bolus of 1 μg/kg fentanyl.

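### Respiratory rate is a sign in the block-adequacy, sevoflurane, rescue-fentanyl and block-failure rules, although ventilation is controlled during surgery

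*Protocol article*

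**What the plan says.** All places are in the Methods of the protocol article.

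- **Interventions.** The reference values are awake values: "The values of the heart rate, noninvasive blood pressure, and respiratory rate before anesthesia induction will be recorded as baseline values". Induction then includes "3 mg/kg propofol, and 0.1 mg/kg vecuronium intravenously". Every child is intubated, and "mechanical ventilation will be controlled to maintain end-tidal carbon dioxide at" 35–40 mmHg.
- **Ultrasound-guided lumbar plexus block group, adequacy.** Besides the ultrasound findings, an adequate block needs "increases in the heart rate, blood pressure, and respiratory rate of less than 15% in response to the skin incision", and rises in the same three signs below 25% during the operation. Neither criterion names a reference value.
- **Same section, sevoflurane.** The concentration goes up by 0.5% when the three signs rise more than 15% from baseline, and down by 0.5% "if the reductions in heart rate, noninvasive blood pressure, and respiratory rate are greater than 15% of the baseline values during the operation".
- **Same section, failure.** "If additional fentanyl is required when the heart rate, blood pressure, and respiratory rate increase by greater than 25% intraoperatively", then "the patient will be recorded as a failure or an inadequate lumbar plexus block". This sentence names no reference value either.
- **Control group.** The sevoflurane rules are the same. A further 1 μg/kg of fentanyl is given "if the heart rate, blood pressure, and respiratory rate increase by greater than 25% of the baseline values during the surgery".
- **Intraoperative anesthetic management and postoperative assessment.** Return of adequate spontaneous breathing appears after the operation, as a condition for extubation.
- **Statistical analysis.** Failed blocks stay in the intention-to-treat analysis and leave the per-protocol set. Sevoflurane dose is a covariate in a logistic regression for emergence agitation.

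**The concern.** A rise in respiratory rate can signal pain or light anesthesia in a child who breathes spontaneously. After a muscle relaxant and under ventilation adjusted to a carbon dioxide target, the rate is mostly what the anesthesiologist has set. Comparing it with an awake rate then says little about nociception or about whether the block works.

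The rules join the three signs with the word *and*, and do not say whether all must cross the limit or any one is enough. Respiratory rate does harm under both readings where the awake baseline applies: it either holds back a needed response or starts an unneeded one.

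At stake is how consistently the anesthetic is given. The Background names low-solubility inhalational agents and pain as two significant predisposing factors for emergence agitation, and these rules govern sevoflurane and intraoperative fentanyl. They are applied by the anesthesiologist, who is not blinded. The block-arm rule also feeds the failure record behind the per-protocol set.

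**Working it through.** The plan gives no figure to reproduce here, so the check is on the logic of the rules, followed by a percentage illustration.

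**Inputs from the document:** limits of 15% (sevoflurane) and 25% (control-arm fentanyl); a step of 0.5%; maintenance at 2% end-tidal sevoflurane. **Assumed, because the document gives none:** set ventilator rate R and awake baseline rate B.

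**1. Logic.** Take a child whose heart rate and blood pressure are both 30% above baseline.

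| Change in respiratory rate | All three signs above 25%? | Any sign above 25%? | Any sign more than 15% below? |
|---|---|---|---|
| −30% | no | yes | yes |
| 0% | no | yes | no |
| +10% | no | yes | no |
| +30% | yes | yes | no |

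Under the all-three reading, a clear rise in two signs draws no rescue fentanyl in the control arm unless the ventilator rate also happens to be high. The same holds for the sevoflurane increase in both arms: in the first three rows respiratory rate is not above its 15% limit. Under the any-one reading, the first row calls for a sevoflurane increase and a decrease at once.

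**2. Any one sign suffices (sevoflurane rules, both arms).** Respiratory rate alone triggers
- a decrease if R < 0.85B, that is, B > R/0.85 = 1.176R;
- an increase if R > 1.15B, that is, B < R/1.15 = 0.870R.

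It triggers nothing only when B lies between 0.870R and 1.176R:

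| Assumed R (/min) | Lower limit R/1.15 | Upper limit R/0.85 |
|---|---|---|
| 16 | 13.9 | 18.8 |
| 20 | 17.4 | 23.5 |
| 24 | 20.9 | 28.2 |

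For example, B = 25 and R = 20 is a change of (20 − 25)/25 = −20%, past the 15% limit for a reduction, with no clinical change in the child.

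**3. All three signs required.** The set rate must exceed 1.15B before sevoflurane can be raised (both arms), and 1.25B before the control-arm fentanyl rule can apply:

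| Assumed B (/min) | R needed, sevoflurane increase | R needed, control-arm fentanyl |
|---|---|---|
| 20 | above 23.0 | above 25.0 |
| 24 | above 27.6 | above 30.0 |
| 30 | above 34.5 | above 37.5 |

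**4. Size of a step.** From 2%, one step is 0.5/2 = 25% of the maintenance concentration. That is the size of any step, justified or not. It is not an estimate of error.

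**5. Rules without a stated reference.** The incision criterion is worded as a response to incision, which most naturally means a change from just before it. If the ventilator rate is held constant, that change is about zero, so respiratory rate adds no information and produces no false trigger. The intraoperative adequacy criterion and the block-failure sentence leave the reference open. The awake-rate figures above are therefore not applied to any of these three.

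**The case against.** Several points on the other side have weight.

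- **Failure is not a mechanical gate.** A reader might infer that block failures would almost never be recorded. The failure sentence depends on additional fentanyl being required, so a clinical decision is part of it, and it names no baseline. The stronger reading does not follow.
- **Control of ventilation may not be complete throughout.** One vecuronium dose is described and no ventilator mode is named, so some spontaneous effort late in surgery is possible. This stands, and is why the rate is called mainly a ventilator setting. It does not make an awake rate a good comparator.
- **The protocol's single-sign rules do not settle the wording.** Atropine for a low heart rate and ephedrine for low blood pressure each treat one abnormality. They do not show how several signs of light anesthesia should combine.
- **The source of the titration rule is not at hand.** The block-arm sevoflurane rule cites a published study, and how the signs combine there cannot be checked.
- **The 15% and 25% limits do not contradict each other.** A reader might infer a conflict, because a rise between them at incision is not adequate by one sentence and not a failure by another. One sentence describes an adequate block; the other says when failure is recorded, without saying that this is the only case. The failed block of the Statistical analysis section most naturally means that record.
- **No bias is shown.** The same signs and sevoflurane limits apply in both arms, and all respiratory rates used above are assumed.

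What remains is that a sign with little meaning under controlled ventilation stands in printed dosing rules, under a conjunction that can be read in two opposite ways.

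**Conclusion.** The point holds and is minor. It is strongest for the sevoflurane rules in both arms and the control-arm fentanyl rule, where the baseline is the pre-induction value: respiratory rate can block a warranted response under one reading and cause an unwarranted step under the other. For the adequacy criteria and the block-failure sentence it is simply uninformative.

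How often this would alter a child's anesthetic cannot be estimated, since the document gives neither awake nor ventilator rates. The conclusion assumes that ventilation is controlled for most of the operation, as the Interventions section indicates.

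A reader might go further and infer that the primary result is biased. The documents do not support that: the intention-to-treat comparison does not depend on the failure record, and no difference between arms in how these signs act has been shown.

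**What to change.** Remove respiratory rate from the intraoperative criteria in the block-group and control-group sections. Keep heart rate and blood pressure, and state whether either one or both must cross the limit. That choice belongs to the clinical team; the document does not decide it.

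The cost is low but depends on the stage of the trial, on which the article is unclear: Study time says it was completed in October 2018, while Trial status says it is recruiting. If recruitment continues, the change affects intraoperative conduct and needs a short amendment. If enrolment is complete, conduct can no longer change. The report should then state how the signs were applied in practice, and the per-protocol analysis should take failed block to mean the failure record described in the block-group section. That record is already required, so no new data are needed.

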### Intraoperative anesthetic management and postoperative assessment

If the heart rate is reduced to less than 50 beats per min during the operation, then 10 μg/kg atropine will be used. If the blood pressure is reduced by greater than 25% of the baseline value, then 0.1 mg/kg ephedrine will be administered. At the end of surgery, sevoflurane will be discontinued, and the fresh gas flow will be increased to 6 l/min.

After completion of the operation, children will be transferred to the PACU and observed until the end of the study period. ECG results, noninvasive blood pressure, and pulse oximetry will also be measured every 5 min. After recovery of adequate of spontaneous breathing, purposeful movement, and eye opening, the endotracheal tube will be removed.

EA will be assessed using the PAED scale (Table 1) [24] at 0, 5, 10, 20, and 30 min after emergence from anesthesia. The PAED score will be documented by the same well-trained doctor, who will be blinded to the allocation group. The PAED score consists of five psychometric items: eye contact with the caregiver, purposeful action, awareness of surroundings, restlessness, and inconsolability. Each item is scored on a 5-point scale (0–4). The maximum score is 20. EA is defined as a PAED score greater than 10 points [25]. Patients with severe EA (PAED score ≥ 13) [24] will be treated with a bolus of 0.5 μg/kg fentanyl. The incidence of EA, frequency of severe EA, and duration of EA will be documented.

**Table 1 Tab1:** Pediatric Anesthesia Emergence Delirium (PAED) scale

1. The child makes eye contact with the caregiver	
2. The child’s actions are purposeful	
3. The child is aware of his/her surroundings	
4. The child is restless	
5. The child is inconsolable	

Items 1, 2, and 3 are reverse scored as follows: 4 = not at all, 3 = just a little, 2 = quite a bit, 1 = very much, 0 = extremely

Items 4 and 5 are scored as follows: 0 = not at all, 1 = just a little, 2 = quite a bit, 3 = very much, 4 = extremely

Scores for each item are summed to obtain a total PAED score between 0 and 20

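### Respiratory rate, mainly a ventilator setting here, should not trigger sevoflurane, fentanyl or failed-block rules; adequate and failed block also leave a gap that matters for the per-protocol set

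*Protocol article*

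**What the plan says.** All places are in the protocol article.

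- **Interventions.** Vecuronium is given at induction, and after intubation "mechanical ventilation will be controlled to maintain end-tidal carbon dioxide at" 35–40 mmHg. Heart rate, blood pressure and "respiratory rate before anesthesia induction will be recorded as baseline values".
- **Ultrasound-guided lumbar plexus block group, sevoflurane.** The 0.5% increase applies "If the increases in heart rate, noninvasive blood pressure, and respiratory rate are greater than 15% from the baseline". The 0.5% decrease applies "if the reductions in heart rate, noninvasive blood pressure, and respiratory rate are greater than 15% of the baseline values during the operation".
- **Same section, rescue and failure.** "If additional fentanyl is required when the heart rate, blood pressure, and respiratory rate increase by greater than 25% intraoperatively", then "the patient will be recorded as a failure or an inadequate lumbar plexus block and also be followed up".
- **Same section, adequacy.** An adequate block needs the needle tip and the local-anesthetic spread seen to be right. The rises in the same three signs must also stay under 15% at incision and under 25% during surgery.
- **Control group.** The sevoflurane rules are the same. Extra fentanyl is given on a rise above 25% in the three signs.
- **Intraoperative anesthetic management and postoperative assessment.** Spontaneous breathing is mentioned only after surgery: "After recovery of adequate of spontaneous breathing, purposeful movement, and eye opening, the endotracheal tube will be removed". Here single signs are used: atropine on heart rate, and ephedrine "If the blood pressure is reduced by greater than 25% of the baseline value".
- **Statistical analysis.** The intention-to-treat analysis keeps failed blocks and the per-protocol analysis removes them. The section does not refer back to either block definition.

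**The concern.** Under controlled ventilation the respiratory rate mostly reflects what the anesthesiologist has set to reach the carbon dioxide target. It says little about pain or depth of anesthesia, and it is compared with a rate taken while the child was awake or at least not yet induced. Joining it by 'and' to two informative signs makes the rules depend on a reading that the text does not fix.

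The anesthesiologist has to choose that reading during the case. It decides when sevoflurane moves, when a control child gets more fentanyl and which block is written down as failed. The last of these decides who leaves the per-protocol set.

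A second, separate problem is that the adequacy definition and the failure record are not complements. Some blocks satisfy neither.

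**Working it through.** There is no stated figure to reproduce, because the point rests on the logic of the rules.

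**Limits.** Let b be the pre-induction respiratory rate and v the intraoperative rate. The 15% and 25% limits are the protocol's. The failed-block sentence names no reference value, so I take the baseline defined under Interventions.

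- All three signs required: the sevoflurane increase needs v > 1.15b, and rescue or a failure record needs v > 1.25b, whatever heart rate (HR) and blood pressure (BP) do.
- Any one sign sufficient: v < 0.85b alone meets the sevoflurane decrease.

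The documents give neither b nor v. With b assumed:

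| Assumed b (per min) | 1.15b (increase) | 1.25b (rescue, failure) | 0.85b (decrease) |
|---|---|---|---|
| 20 | 23 | 25 | 17 |
| 30 | 34.5 | 37.5 | 25.5 |
| 40 | 46 | 50 | 34 |

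Turned round, for an assumed ventilator rate v, the respiratory part of each rule is met as follows:

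| Assumed v (per min) | Decrease: b > v/0.85 | Increase: b < v/1.15 | Rescue, failure: b < v/1.25 |
|---|---|---|---|
| 16 | 18.8 | 13.9 | 12.8 |
| 20 | 23.5 | 17.4 | 16.0 |
| 25 | 29.4 | 21.7 | 20.0 |

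These figures show where the limits lie. They do not show how often they are crossed.

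**Three cases through both readings.**

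| Case | All three | Any one |
|---|---|---|
| HR +30%, BP +30%, v = b | No rule met | Increase, and rescue or failure |
| HR +20%, BP +20%, v = 0.80b | No rule met | Increase and decrease together |
| HR 0%, BP 0%, v = 0.80b | No rule met | Decrease, from the ventilator rate alone |

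So the all-three reading stops the upward rules and the failure record from firing on HR and BP alone. The any-one reading leaves those rules working and breaks only the decrease. The increase and decrease rules are worded in parallel, so the text gives no ground for reading one as 'any' and the other as 'all'.

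**Adequacy against failure, with v = b and no rescue fentanyl.**

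- HR +20% at incision: over the 15% adequacy limit, but under the 25% failure limit. Neither adequate nor failed.
- Poor spread, with HR and BP +10%: not adequate on imaging, and no failure recorded. Again neither.

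Both results hold on either reading of 'and'.

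**The case against.** **The ventilator premise is not absolute.** Only an induction dose of vecuronium is stated, with no maintenance relaxant, and the length of surgery is not given. A child may breathe over the ventilator later in the case, and then the rate carries some information. This stands, and it is why I say 'mainly' a ventilator setting. It does not make the rate a sound trigger for the rest of the operation.

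**A reader might infer that no reading gives usable rules.** The documents do not support that. Under 'any one', the sevoflurane increase, rescue fentanyl and the failure record all work through HR or BP. Only the decrease misfires, and only when v is below 0.85b.

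**A reader might infer that failed block is undefined in the analysis.** It is not. The block-group section is the only place that records a failure, so it is the natural source. A missing cross-reference in a condensed article is editorial. What remains is the gap between the two definitions.

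**A reader might infer that the sevoflurane covariate in the logistic regression is mismeasured.** That does not follow. Data collection and management records the sevoflurane dose, so the model would use what was delivered, whatever prompted it.

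**A reader might infer bias in the primary result, since the person choosing the reading is unblinded.** The written sevoflurane rules are the same in both arms, and nothing in the documents gives a direction or size.

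**Conclusion.** The point holds and is minor. Respiratory rate should not sit in the adequacy, sevoflurane, rescue-fentanyl or failed-block rules under controlled ventilation. Taken literally as all three signs, the upward rules cannot respond to HR and BP alone. Taken as any one, the sevoflurane decrease can be set off by the ventilator and can contradict an increase.

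The gap between adequate and failed block matters only for the per-protocol set. The membership of the primary intention-to-treat set is unchanged.

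The number of children affected, and the direction and size of any effect, cannot be derived from the documents. The conclusion assumes that the ventilator determines the rate for most of the case and that changes are judged against the pre-induction baseline. The rates of 16 to 40 per minute used above are illustrations only.

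**What to change.** Drop respiratory rate throughout, and state the connective in each rule.

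1. **Adequate block:** correct needle tip and spread, and rises in both HR and BP below the limits (15% at incision, 25% during surgery). Do not write 'either' here: HR +40% with BP +5% would then pass.
2. **Failed block, for the per-protocol set:** rescue fentanyl required for a rise above 25% in either HR or BP. Fix this before the sealed block records described under Blinding are opened. Excluding every block that is not adequate should be a sensitivity analysis only.
3. **Triggers, only if recruitment is open** (Study time gives completion in October 2018, while Trial status says recruiting). In both arms, give rescue fentanyl when either sign rises more than 25%. Step sevoflurane when either sign moves more than 15% and the other has not moved more than 15% the opposite way. Deleting respiratory rate alone would leave 'and' unresolved, and a bare 'or' would let HR +20% with BP −20% call for both steps.

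**Cost.** The change is to wording only. HR and BP are already recorded every 5 min, block details are recorded and the fentanyl dose is collected. The downside is that the per-protocol set may shrink, and in the block arm only, because these post-randomization exclusions have no control counterpart. That is why the wider exclusion stays a sensitivity analysis.
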